***Termination of the study***

Subjects will be requested to withdraw from the study if any of the following occurs:

1. Persistent corneal staining (> Grade 2 in Efron’s scale)
2. Unaided monocular vision worse than 6/9 in either eye (only for full correction ortho-k subjects only)
3. Non-compliance with study protocol (e.g. wear contact lenses during the discontinuation period or rarely use ortho-k lenses during the lens wear period)

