**Figure 1. Data collection visits in the experimental phases in the discontinuation study.**

*Data collection visits*

*Phase I*

- Visit I-0 – Commencement of Phase I for all subjects; Commencement of RS period for Group OKd (Experiment 1)
- Visits I-1, I-3, I-6, I-7: about one, three, six and seven months after Visit I-0

*Phase II*

- Visit I-7 – Commencement of Phase II for all subjects; Commencement of RS period for Group OKd (Experiment 1) and all subjects in Experiment 2
- Visits II-1, II-3, II-6, II-7: about one, three, six and seven months after Visit I-7

**Experiment 1.** *Discontinuation of lens wear in existing ortho-k children*

The objective of this study is to compare eyeball elongation in existing ortho-k subjects who stopped lens wear with subjects who continued ortho-k lens wear and control subjects wearing glasses.

Figure 1 shows the required visits for the duration of the experiment for each group of subjects.

In this experiment, subjects who have completed the ROMIO, TO-SEE and HM-PRO studies will be invited to participate. All spectacle-wearing control subjects will be invited to continue as control subjects. Ortho-k subjects will be randomly assigned into Groups OKc or OKd.

All subjects will be followed up for a period of 14 months.

- Group C will continue to wear spectacles for the duration of the experiment
- Group OKc will continue lens wear for the duration of the experiment
- Group OKd will be required to discontinue lens wear for 6 (+1*) months (and wear single-vision spectacles Phase I) and then resume ortho-k lens wear for another 6 (+1*) months (Phase II). *The first month (*) of each phase (See Figure 1), where indicated, is the RS (Refraction Stabilization) period to allow stabilization of refractive errors.*

*Group OKd*

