At the beginning of Phase I (Spectacle-wear phase), subjects will be required to wear single-vision spectacles to aid distance vision in the RS period. They are required to use their old spectacles which should be +/– 0.50DS in sphere and +/– 0.50 DC in cylinder from the refraction determined at the time of visit, otherwise, new spectacle lenses will be ordered. They will be followed up weekly until stabilization of refractive errors has been achieved and the stabilized refraction will be used for the prescription of the spectacles which will be delivered at Visit I-1. Once the refraction has stabilized, all children will be required to wear fully-corrected spectacles in the daytime during Phase I. They will be excluded if they regularly use any kind of contact lenses during Phase I.

New ortho-k lenses for these subjects will be ordered one month before the end of Phase I (ie. at Visit I-6) and dispensed at the end of Phase I (Visit I-7) before commencing Phase II (see Table 1).

In Phase II (Ortho-k phase), subjects are required to wear the ortho-k lenses every night unless otherwise instructed by their examiner. They need to attend the ortho-k aftercare visits as scheduled. Complimentary contact lens solutions and lens accessories (Table 2) will be supplied during the treatment. They have to keep an ortho-k journal everyday. Single-vision spectacles may be needed to aid distance vision during the RS period.

Cycloplegic data collection will be conducted at the beginning of each phase, at the end of RS period (for Group OKd only) and at the end of each phase. Subjects will be required to come back for the regular non-cycloplegic data collection visits after RS period. Change in axial length in the 6 months following stabilization of refractive errors for each Phase will be determined and compared within subjects and between groups. The whole study period for each subject will last for about 14 months.

*Group C and Group OKc*

Subjects will wear their habitual spectacles/ortho-k lenses at the commencement of Phase I, before Visit I-1. New glasses will be made based on Rx determined at Visit I-0 and delivery of new glasses will be at Visit I-1 and if indicated (based on data collected at Visit I-6), at Visit I-7 before commencing Phase II. Note that there is no RS period for these two groups of subjects, but cycloplegic and non-cycloplegic data correction visits will be same as Group OKd.

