***Ortho-k lenses, solutions and spectacles lenses***

*Ortho-k lenses*

Menicon Z Night and Night Toric lenses will be used in this study. Lenses to be ordered will be determined by the Easy Fit software (based on topographic data captured by the Medmont corneal topographer, the manifest refractive error and the corneal diameter). Full correction will be attempted for myopia ≤ 4.50D and partial correction targeted for 4.00D will be applied for myopia  4.50D.

- All ortho-k subjects who agreed to be randomized in Experiment 1 and all subjects in Experiment 2 will be provided with the required ortho-k lenses during the study period(s) as indicated.
- Subjects who refused to be randomized into Group OKd can participate in DOEE study as subjects in Group OKc if they pay for the lenses used during the experimental period (these will not be complimentary lenses but will be ordered via our clinic, ie. payment of lenses will go to our Optometry Clinic). They have to agree to return for the scheduled aftercare and data collection visits and each subject will receive a pair of complimentary lenses at the end of the study period.

*Contact lens solutions & accessories*

All the solutions used in this study are shown in Table 2. All solutions have to be replaced at least once every 2 months.

- Group OKc – Subjects will be required to purchase all solutions required (except for O2 Care) from our Clinic
- Group OKd in Experiment 1 and all ortho-k subjects in Experiment 2 –Complimentary contact lens solutions will be provided
- All subjects will be given complimentary flat lens cases, SP vial for weekly protein removal and O2 Care daily cleaning during the study period.

*Spectacle lenses*

Spectacles are required during the discontinuation period and may be needed in the first 2 weeks of the lens wear period. Subjects will be asked to keep their habitual spectacles. Complimentary spectacles lenses will be provided if indicated, provided that subjects use their own frames. New spectacle lenses will be prescribed once the refraction has stabilized during the RS period (where appropriate). Low refractive index *spherical* lenses will be prescribed for low myopes (myopia < 4.50D) and high refractive index lenses will be used for high myopes ( 4.50D) and high astigmatism ( 2.00DC).

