**Table 1. Data collection visits for Experiments 1 & 2.**

| Cycloplegic | Non-cycloplegic | Description | Remark |
| --- | --- | --- | --- |
| Phase I |  |  |  |
| I-0 |  | Baseline |  |
| [RS period: Weekly visits (for Group OKd subjects) to determine stabilization of Rx. Order new ortho-k/spectacles for the 3 groups of subjects for delivery at Visit I-1 (Rx for Group C and OKc should not be more than 1 month old)] | | | |
| I-1 |  | End of RS period in Phase I (3 days)  (*same visit as I-0 for Experiment 2 as there will be no RS period) | - Delivery of glasses for Group C and ortho-k lenses for Group OKc - Delivery of glasses for Group OKd and all subjects in Experiment 2 |
|  | I-3 | 3 (1 week) after commencing Phase I |  |
|  | I-6 | 6 months (1 week) after commencing Phase I | - Order new ortho-k lenses/spectacles based on updated Rx for the 3 groups of subjects for Visit I-7 where indicated |
| I-7 |  | 7 months (1 week) after commencing Phase I |  |
| Phase II |  |  |  |
| II-0 |  | Equivalent to Visit I-7 | - Glasses for Group C and ortho-k lenses for Group OKc (if deemed necessary) - Ortho-k lenses for Group OKd and all subjects in Experiment 2 |
| II-1 |  | End of RS period (3 days) |  |
|  | II-3 | 3 (1 week) after commencing Phase II |  |
|  | II-6 | 6 months (1 week) after commencing Phase II |  |
| II-7 |  | 7 months (1 week) after commencing Phase II |  |

RS - Rx-Stabilization

Group C – Control group in Experiment 1

Group OKc – Ortho-k subjects who will continue ortho-k lens wear for the whole experiment period in Experiment 1

Group OKd – Ortho-k subjects who will discontinue ortho-k lens wear in Phase I and resume ortho-k lens wear in Phase II in Experiment 1

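### Withdrawal rules end study participation, rule 2 names no period and conflicts with planned discontinuation in Group OKd, and no axial length is collected after a rule is met

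*Protocol*

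**What the plan says.** The section Termination of the study opens: "Subjects will be requested to withdraw from the study if any of the following occurs". Three rules follow.

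- Rule 1 concerns persistent corneal staining and names no group or period.
- Rule 2 reads "Unaided monocular vision worse than 6/9 in either eye (only for full correction ortho-k subjects only". It names a type of child but no period.
- Rule 3 is non-compliance. Its examples do name periods: "wear contact lenses during the discontinuation period or rarely use ortho-k lenses during the lens wear period".

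The Experiment 1 text adds a further exclusion for Group OKd: "They will be excluded if they regularly use any kind of contact lenses during Phase I". It does not say whether this means exclusion from the study or from an analysis.

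Elsewhere the protocol describes what Group OKd is meant to do. Under Experiment 1, "Group OKd will be required to discontinue lens wear for 6 (+1*) months". At the start of Phase I, "subjects will be required to wear single-vision spectacles to aid distance vision in the RS period". The spectacle lens text says: "Spectacles are required during the discontinuation period and may be needed in the first 2 weeks of the lens wear period". The legend to Table 1 still calls these children ortho-k subjects: "Ortho-k subjects who will discontinue ortho-k lens wear in Phase I and resume ortho-k lens wear in Phase II".

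Full correction is defined in the lens section by myopia of 4.50 D or less; higher myopia receives partial correction. Axial length is the primary outcome (Examination procedures).

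**The concern.** There are three linked problems.

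1. **Contradiction.** Rule 2 has no time limit, and Group OKd children with myopia up to 4.50 D are, by the protocol's own labels, full-correction ortho-k subjects. Their assigned Phase I treatment is expected to leave them needing spectacles for distance. The protocol therefore both requires that state and lists poor unaided vision as a reason to leave.
2. **Unequal action.** If rule 2 is meant for lens wear only, then in Phase I it can remove children from Group OKc but not from OKd or from the control group. Phase I holds the contrast between stopping and continuing. A withdrawal rule that acts in one arm only, on a measure that may move with the outcome, can distort that contrast.
3. **Lost outcome data.** Rule 3 and the contact lens exclusion remove randomised children because they departed from their allocation, and removal is from the study. If axial length is not measured afterwards, the data needed for a comparison as randomised do not exist. A statistical analysis plan can define populations, but it cannot recover measurements that were never taken.

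**Working it through.** **Step 1: the plan's own sample size.** Inputs from Subject number: difference 0.12 mm, SD 0.17 mm, alpha 0.05, power 80%, 33 completers per group.

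- Normal formula, two-sided: n = 2 × (1.96 + 0.84)² × 0.17² / 0.12² ≈ 31.5, so 32. The t-test version gives 32.49, so 33. The stated figure reproduces.
- Power at 33 per group is 0.82 (normal) or 0.81 (t-test).
- Dropout of 15%: 66 / 0.85 = 77.6, so 78; 33 / 0.85 = 38.8, so 39. The planned 80 and 40 cover this.

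The sample size is not in question.

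**Step 2: who can meet rule 2, and when (Experiment 1).**

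| Group | Literal reading, Phase I | Lens-wear-only reading, Phase I | Lens-wear-only reading, Phase II |
|---|---|---|---|
| Control | no | no | no |
| OKc, full correction | yes | yes | yes |
| OKd, full correction | yes, through the assigned discontinuation | no | yes |
| OKc or OKd, partial correction | no | no | no |

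The trigger would be seen. Table 4a schedules habitual or unaided acuity at every visit type, and its supplement specifies unaided for the ortho-k group and habitual for controls. Even the lens-wear-only reading leaves a conflict, because spectacles may be needed early in Phase II. The same applies to Phase II of Experiment 2, where Table 3 caps myopia at entry at 4.50 D.

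**Step 3: is the rule related to the outcome?** Subject number equates 0.12 mm with 0.33 D. Under a fixed lens, more axial growth means more residual myopia and worse unaided vision. Against this, poor lens response also worsens unaided vision, and Table 1 lists ortho-k lenses for OKc at I-1 and again at I-7 if needed. A relation is plausible, but the documents do not give its strength.

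**Step 4: ranges, on assumptions only.** The documents give neither a removal rate nor the difference in growth between removed and remaining children.

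- *Precision.* Take 33 completers in one arm and an extra fraction lost from the other, beyond planned dropout. Power = Φ(0.12/0.17 × √(n₁n₂/(n₁+n₂)) − 1.96). Losses of 10%, 20%, 30% and 50% give 0.80, 0.77, 0.74 and 0.65.
- *Selection.* If a fraction q is removed and its mean growth is d above that of the children who remain, the completer mean is too low by q × d. For q = 10% and d = 0.05 mm this is 0.005 mm; for q = 30% and d = 0.17 mm it is 0.051 mm. That is 4% to 43% of 0.12 mm.

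The 0.12 and 0.17 mm are 12-month figures, whereas each phase compares 6 months of growth, so these ranges show scale only.

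**Step 5: after withdrawal.** No section provides for axial length visits once a child has met a rule. The visits themselves are already scheduled for every child to II-7 (Table 1).

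**The case against.** The strongest reply is that nobody would apply rule 2 to Group OKd in Phase I. Full correction is a property of a worn lens, these children wear none, and several sections require them to stop lenses and attend I-1 to I-7. Applying the rule would abolish the arm under study, and children are in any case requested, not compelled, to withdraw. This stands as a statement of likely intent. It does not remove the gap: rule 3 names its periods and rule 2 does not, and the conflict early in lens wear remains.

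A reader might infer that all full-correction OKd children would be lost, or that faster-growing eyes leave OKc and make continued wear look better than it is. The documents support neither as a finding.

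- The two do not add up. The first needs the literal reading; the second needs the lens-wear-only reading, under which OKd is untouched in Phase I.
- No headcount follows, because the protocol does not say how many recruits will be full correction.
- The second treats poor unaided vision as a marker of growth. Lens response and the renewals at I-1 and I-7 weaken that, and no rate or correlation is given.

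It is also fair that only rule 2 is restricted by group, that the control group is not randomised, that an unaided-vision rule has no natural meaning for spectacle wearers, and that rule 3 and the contact lens exclusion aim at gross departures. The choice of analysis population may be settled in an analysis plan not shown here. The loss of measurements cannot be.

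**Conclusion.** The point holds in limited form. Rule 2 conflicts with the Experiment 1 text, the spectacle lens text and Table 1, and the passages must be reconciled. On the likely intended reading it acts in Phase I on OKc only and could be related to axial growth. Less apparent growth in OKc is the plausible direction, but its size cannot be computed from the documents; 0.005 to 0.051 mm is an illustration under assumed inputs, before any softening by lens renewal. The firmest part is the loss of outcome data: rule 3 and the contact lens exclusion remove randomised children for leaving their allocation, and nothing provides for measuring them afterwards. This should be changed, because the loss cannot be repaired at analysis. The planned sample size is not affected.

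**What to change.** 1. State in which periods rule 2 applies, and reconcile it with the Experiment 1 text, the spectacle lens text and Table 1. The clinical criteria remain the investigator's decision.
2. Separate stopping lens wear from leaving the study. Children who meet any rule, or who do not comply, still attend the scheduled axial length visits to II-7 unless consent is withdrawn. Say explicitly that the contact lens exclusion for Group OKd does not end measurement.
3. Compare OKc with OKd as randomised, using all available axial lengths. Restrict this comparison to children actually randomised: the lens section lets children who refuse randomisation to OKd enter OKc by paying for their lenses, and these should be left out of it. Give the compliers-only result as supportive.

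The cost is protocol wording, since the visits are already scheduled. The small downside is that children off their allocation dilute the estimate somewhat.

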***Consistency of management***

- Standard fitting protocol will be used to minimize the effect of inter-practitioner difference.
- Both oral and written instructions will be given to the subjects to increase the consistency in lens handling as well as patient compliance.
- Subjects will be asked to keep an ortho-k journal to keep track of lens wear schedule, incidence of lens binding and problems encountered by the subjects. This information will be useful for the assessment of compliance and helpful to the practitioners in giving proper advice in the presence of complication.
- Contact lens solutions will be given and/or purchased (depending on which group) from our clinic and should be replaced at least bimonthly to:
  1. compensate subjects for their time and increase the incentive of the subjects to remain in the study,
  2. encourage regular replacement of contact lens solutions, and
  3. encourage subjects to return for bimonthly visit.

***Confidentiality***

Only members in this project are allowed to have access to the collected information. Results from the current study may be published but no personal information will be disclosed.

***Subject number***

From the current ROMIO study, the mean different and SD of the change in axial length in the ortho-k and the control groups who have completed the 12-month lens wear timeline are 0.12 and 0.17mm respectively. To detect a 0.12mm (equivalent to 0.33D) between-group difference for an alpha value of 0.05 and 80% power in 12 months, a sample size of 33 is required for each group.

For Experiment 1, we aim to have at least 66 ortho-k and 33 control subjects completing this study. Allowing for about 15% dropout, we will recruit 80 ortho-k and 40 control children.

*The ROMIO, HM-PRO and TO-SEE studies are ortho-k projects currently being conducted in PolyU. ROMIO and HM-PRO studies are targeting 30 ortho-k and 30 control subjects each and TO-SEE study is targeting for 30 ortho-k subjects. Hence, there will be 90 potential ortho-k and 60 control subjects and so we do not expect difficulties in recruiting the required subjects for this experiment*.

For Experiment 2, we aim to have at least 70 (35 younger and 35 older) subjects completing the study. Allowing for dropouts (including unsuccessful lens wear), we will recruit 90 (45 younger and 45 older) children.

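### Experiment 1's 80% power is calculated on a 12-month difference and SD, but the planned outcome is 6-month change and Group OKd is off lenses for only 6 (+1) months, so the figure is not supported for any OKd contrast

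*Protocol*

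**What the plan says.** The Subject number section takes its inputs from ROMIO ortho-k and control children "who have completed the 12-month lens wear timeline are 0.12 and 0.17mm respectively" (mean difference, then SD). It sizes the study on these: for a 0.12 mm "between-group difference for an alpha value of 0.05 and 80% power in 12 months, a sample size of 33 is required" per group. For Experiment 1, "we aim to have at least 66 ortho-k and 33 control subjects completing this study", that is, 33 in each of OKc, OKd and control if the ortho-k children split evenly.

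The Experiment 1 text, under Group OKd, sets the outcome to be compared: "Change in axial length in the 6 months following stabilization of refractive errors for each Phase will be determined", with comparison both within subjects and between groups. On treatment it says "Group OKd will be required to discontinue lens wear for 6" (+1) months, after which these children resume ortho-k for another 6 (+1) months. The Subjects section repeats this.

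The first primary objective, under Objectives, compares children who stopped lenses with those who continued and with spectacle-wearing controls.

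**The concern.** The sample size and the outcome are on different time bases. Both the difference and the SD describe a year of growth, while the outcome covers half a year. Neither can be carried to the shorter window unchanged. The difference depends on how the effect builds up over time, and the SD depends on how strongly a child's growth in one half-year is related to growth in the next. The protocol addresses neither.

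The treatment schedule points the same way. OKd and OKc differ in treatment only during Phase I. In no 12-month window is OKd continuously off lenses, so no OKd comparison matches the ROMIO contrast behind the 80%.

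OKd versus OKc is the comparison that Experiment 1 sets up by randomization, and it answers the question that motivates the study. If it showed no difference, readers would take that as the result of a trial with 80% power for this question, although that power was never calculated for it.

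**Working it through.** **Inputs from the protocol (Subject number):** difference 0.12 mm and SD 0.17 mm, both for 12-month change; alpha 0.05; power 80%; 33 completers per group. Sidedness is not stated; two-sided reproduces the stated number, whereas one-sided would need only about 26 per group.

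**Step 1: reproduce the plan's figure.** Two-sample t-test, two-sided. Standardized difference d = 0.12/0.17 = 0.706. The solution is n = 32.5, rounded up to 33 per group, with power 80.6% at 33. The arithmetic is right for a 12-month difference.

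**Step 2: what a 6-month window needs.** The protocol gives no 6-month difference or SD, so the following are assumptions.

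- Difference: with even accrual, 0.12/2 = 0.06 mm.
- SD: let the two half-year changes have equal SD s and correlation r. Then 0.17² = 2s²(1 + r), so s = 0.17/√(2(1 + r)).

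**Step 3: power at 33 per group for 0.06 mm, and the difference detectable with 80% power.** At 33 per group, 80% power requires d = 0.700, so the detectable difference is 0.700 × s.

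| Half-year correlation r | s (mm) | d = 0.06/s | Power | Detectable difference (mm) |
|---|---|---|---|---|
| 0 | 0.120 | 0.499 | about 52% | 0.084 |
| 0.5 | 0.098 | 0.611 | 69% | 0.069 |
| 1 | 0.085 | 0.706 | 81% | 0.060 |

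**Step 4: the case of an unchanged SD.** Setting s = 0.17 gives d = 0.06/0.17 = 0.353 and power 29%. In the model of step 2 this requires 1 + r = 1/2, so r = −0.5: children who grow more in one half-year would have to grow less in the next. Nothing in the protocol suggests this, so 29% marks an extreme case and is not used as the lower end of the range.

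**Step 5: the case of a front-loaded effect.** If more than half of the 12-month difference arises in the first 6 months, then with SD 0.12 mm:

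- 0.08 mm: d = 0.667, power 76%
- 0.09 mm: d = 0.75, power 85%

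**The case against.** The best defence is that the Introduction reports the myopia-control effect as greatest in the first six months of treatment. Even accrual may then be pessimistic, and step 5 shows that power could be near or above 80%. This stands as a reason not to call the trial underpowered. It does not rescue the stated figure. The sample size section does not use the argument. The Introduction describes children starting lenses, whereas the Experiment 1 children have completed two-year studies and OKd is stopping. The Introduction also says it is unknown whether the effect dissipates on stopping.

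A second objection is that all groups are followed for 14 months with common data collection visits, so elongation over about 12 months can be compared between OKd and the others. That is correct, and a reader should not infer that no such comparison is possible. But over that period OKd is partly in spectacles and partly in lenses, so it is not the contrast from which 0.12 mm was taken, nor is it the 6-month outcome that the protocol names.

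A reader might also infer that the 80% can at least be kept for OKc versus control over the whole follow-up, where neither group changes treatment. The window length is then about right, but the protocol does not show that a first-year difference carries over to children who have already completed two years. That pair is also not a randomized comparison, and it says nothing about the OKd contrasts.

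**Conclusion.** The concern holds as a mismatch of time base. The 80% power with 33 per group belongs to a 12-month ortho-k versus control difference. It is not supported for OKd versus OKc or OKd versus control on the 6-month outcome that the protocol sets.

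The size depends on figures that the protocol does not give. Under even accrual and a half-year correlation between 0 and 1, power for 0.06 mm is about 52% to 81%, and it stays at about 80% only when the correlation is at or close to 1. Under front-loading of 0.08 to 0.09 mm with SD 0.12 mm it is about 76% to 85%.

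Two stronger readings go too far. The documents do not show that the true power is below 80%, only that 80% has not been shown. They also do not show an arithmetic error: 33 per group is correct for the inputs used.

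**What to change.** In Subject number, restate the power or the detectable difference for the 6-month Phase I contrasts of OKd with OKc and with control, at 33 completers per group, and name those contrasts. Use a 6-month difference and SD from ROMIO if they are available. If not, state that 33 per group detects about 0.06 to 0.084 mm over 6 months with 80% power (SD 0.085 to 0.120 mm), with about 52% to 81% power for 0.06 mm, and give the assumptions: even accrual and a half-year correlation of 0 to 1. If front-loading is to be relied on, say so and justify it for stopping lenses. Do not attach the 12-month 80% figure to any OKd contrast.

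The cost is a change of wording, with no added children or visits. The stated power for the main contrasts may become less favourable.
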